#### Environmental support and social engagement

Housing and living situation is assessed using several questions. The interviewer rates at the start of the home interview the type of dwelling (apartment block with or without elevator, row house, semi-detached or detached house). Participants are asked how many years they have lived in the same home, about their living situation (alone, with spouse, with children or grandchildren, with relatives, siblings or other people) and home ownership [27].

Perceived safety of the neighborhood is assessed with the question “Do you fear anything when moving through your neighborhood?”. If yes, participants are asked to specify their fear and to indicate whether the fear made them avoid moving in the neighborhood with response options 1) no, 2) yes, but only at night, and 3) yes.

Data on the use and perceptions of the neighborhood environment and beyond is gathered using an interactive internet-based softGIS or PP-GIS questionnaire (Maptionnaire, Mapita LTD, Helsinki, Finland) [50]. Participants are asked to locate, on a digital map, places where they have been physically active multiple times in the past month (outdoor sports facilities, indoor sports facilities, outdoor recreational areas). Similarly, participants are asked to locate other places motivating them to move outdoors in the neighborhood or beyond (e.g. nature, places to rest, routes, stores, services, and events) for multiple times in the past month. Follow-up questions specify the location, the frequency of visiting, and the mode of transportation used to get to the location. In addition, participants are asked whether they avoided any locations due to issues related to routes, safety, and other reasons in the past month, specifying the object and the occasions, and whether in general they perceive any environmental barriers that hinders their outdoor mobility (e.g. poor street conditions, hilliness, dangerous crossroads and lack of places to rest), specifying the barrier and the frequency of exposure. Finally, participants are asked to define their neighborhood as a polygon, and to locate one place (beyond their home) that gives them pleasure, specifying the object and the frequency of visiting the location. GIS will be used to construct an activity-space of each participant based on reported locations [adapted from [51]]. Features of the objectively assessed environment will be studied in participants’ individual activity-space and the neighborhood they defined as well as in spatial areas defined by network or circular buffers around participants’ home. Participants’ home addresses will be derived from the population register and geocoded in the GIS system. Features of participants’ home environment will be obtained from freely available digital maps (e.g. land use, street network, and services) and virtual audits, which utilize existing online virtual imagery resources (e.g. Google street view) to assess street level characteristics [adapted from [52, 53]].

Socioeconomic status. Education is assessed by asking participants to report the total number of years of education they completed, and by choosing their highest educational attainment from a list, which includes seven alternatives: one (less than primary school), two (primary school), three (middle school or folk high school), four (vocational school), five (secondary school), six (high school), and seven (university degree) [54]. Occupation is assessed by asking participants to report their longest-held occupation and their most recent occupation. The resulting occupations will be classified according to the Statistics Finland’s Classification of Occupations [55], which is based on the International Standard Classification of Occupations ISCO-08 by the International Labour Organization. Participants are asked to rate their self-perceived financial situation on a five-point scale ranging from one (very good) to five (very poor).

Feeling of loneliness is asked with a single question: “How often do you feel lonely?” The response options are rated on a four-point scale: one (very rarely/never), two (rarely), three (often), and four (almost always) [56]. Social relationships and contacts are assessed with questions relating to the participants’ marital status and the frequency of contacts with children and other relatives, close friends, and other acquaintances. The response options for the frequency of contacts are rated as follows: one (daily), two (weekly), three (monthly), four (a few times a year), five (rarely or not at all), and six (not having any children or other relatives/friends/acquaintances) [27]. Moreover, participants are asked whether they have someone with whom they regularly run errands or enjoy the outdoors.

Provision of social support is assessed with a single questions related to volunteer work and informal care provision. Volunteer work is asked with the question “Do you volunteer for some organization, municipal, congregation, etc.?” with response options: one (daily or almost daily), two (approximately once a week), three (approximately once a month), four (few times a year), five (rarely), and six (not at all). Informal care provision is asked with the question “Do you take care of another person needing assistance in daily life due to illnesses or disabilities?” [27]. Caregivers are also asked whether they live in the same home as the care receiver (yes/no) and how often care is generally provided. The response options for the latter question are: one (almost round-the-clock), two (daily), three (few times a week), four (once a week), five (two to three times a month), and six (once a month or less frequently).

Current most important personal hobbies are asked with a single open-ended item question “What are your most important hobbies?” Participants can report as many hobbies as they want.

Perceived age discrimination is assessed with a single item “During the previous year, have you experienced that you have been discriminated or placed in a disadvantaged position compared to other people due to your age (e.g. in offices, health care organizations, or in everyday life)?” The response options are: one (not at all), two (only a little), three (to some extent), four (quite a lot), and five (very much) [adapted from [57]].

#### Physical and sensory function

Maximal isometric handgrip strength is measured on dominant side both in the home interview and in the research center. Handgrip strength has been shown to be a good indicator of general functional status [58]. *During the home interview*, handgrip strength is measured with a hand-held adjustable dynamometer (Jamar Plus digital hand dynamometer, Patterson Medical, Cedarburg, WI, USA), and expressed in kg [58]. The measurement is done in a seated position with the elbow flexed in an angle of approximately 90 degrees. After a practice trial, three to five short maximal contractions with 30 s of rest in-between are conducted. *In the research center,* maximal isometric handgrip strength is measured in a sitting position using an adjustable dynamometer chair (Faculty of Sport and Health Sciences, University of Jyvaskyla, Jyväskylä, Finland), and expressed in Newton [34]. A dynamometer is fixed to the arm of the chair. After a practice trial, the test is performed at least three times until no further improvement occurs, with an inter-trial rest period of 1 min. In addition, maximal isometric knee extension strength is measured in a sitting position using an adjustable dynamometer chair (Metitur LTD, Jyväskylä, Finland), and expressed in Newton [34]. Knee extension strength of the dominant leg is measured at a knee angle of 60 degrees from the fully extended leg towards flexion. The ankle is attached to a strain-gauge system. After a practice trial, the test is performed at least three times until no further improvement occurs, with an inter-trial rest period of 1 min. In the research center, the calibration of the dynamometers is checked daily before use. During each maximal contraction of 2 to 3 seconds, participants are strongly encouraged to exhibit the best possible force. For each test, the best result will be used as the measure of maximal strength in the analyses. The test-retest reliability of the handgrip and knee extension strength test with a 2-week interval has been found to be good in our research center [34].

Reaction time and sensory motor speed are assessed first with a simple finger movement task, followed by a complex finger movement task [59]. The seated participant holds index finger of the dominant hand resting on the rest button in the middle. The participant will move the finger as soon as possible to the button closest to the light, when it switches on. First, the simple reaction time test is conducted and then a more complex test, where any of the seven lights switches on randomly. Reaction time and movement time are measured in milliseconds. The simple and complex tasks are each repeated 12 times. The average times of the final five correctly performed tasks will be used as the result.

Lower-extremity physical performance is objectively assessed in the participant’s home by the Short Physical Performance Battery (SPPB) [60–62]. The battery comprises tests on standing balance, walking speed over a 3-m distance, and the ability to rise from a chair. Each task is rated from zero to four points according to established cut-off points [61, 62], higher scores indicating better performance. Participants unable to perform a test due to mobility-related limitations will be assigned a score of zero for each respective test. A sum score will be calculated (range 0–12), when at least two tests are completed.

Ten-meter walking speed is assessed in the laboratory corridor. The time to walk ten meters with habitual and maximal speed is measured using photocells (Faculty of Sport and Health Sciences, University of Jyvaskyla, Jyväskylä, Finland) and a hand-held stopwatch (for cohort comparisons) and walking speed expressed in m/s will be calculated. On their first walk, participants are instructed to walk at their habitual speed, that is, the speed they would use when running errands [63]. On the second walk, participants are instructed to walk as fast as possible, without compromising safety, for the maximal test [64]. In both tests, five meters is allowed for acceleration, and the walking stops well past the finish line. Participants wear walking shoes or sneakers and are allowed to use a walking aid if needed. The test-retest precision of the maximal walking test with a one- to two-week interval has been shown to be good in our research center [65].

A modified six-minute walking test with a usual walking speed is used to assess walking performance, exercise tolerance and cardiovascular response to exercise [47, 66]. Usual, self-paced walking speed rather than maximal speed ensures the safety of the older participants and promotes continuous walking performance over the duration of the test [47]. Participants are allowed to use a walking aid, if needed. The test is performed in an indoor corridor. Traffic cones are placed at both ends of the course 19.66 m apart, and tape indicates the bend with a 0.30 m radius, resulting in a 40-m lap. Photocells (Faculty of Sport and Health Sciences, University of Jyvaskyla, Jyväskylä, Finland) are placed 18.0 m apart and 0.83 m from each end to record lap times. The total distance walked by participants in 6 min is measured.

*During the six-minute walk test,* gait characteristics are assessed using wearable sensors. Participants are asked to wear five sensors (NGIMU, x-io Technologie Limited, UK) that sample three-dimensional accelerations, gyrations and magnetic field at 400 samples per second during the gait assessment. Sensors are attached to both legs with elastic Velcro straps: above the lateral malleolus and on the anterior aspect of the mid-thigh (co-localized with the taped-on accelerometer used to record physical activity). The fifth sensor is worn on the mid back line at the L4 to S1 level depending on anatomy of the participant. Step or stride rate [67], stance and swing duration [68], and multiscale entropy [67, 69] will be assessed from each of the applicable sensors, and from the thigh-worn accelerometer and the chest-worn accelerometer. Furthermore, we will explore whether age- and functional capacity -related changes in gait can be detected. In addition, gait characteristics will be identified *based on multiple day accelerometry recordings*, enabling comparison with laboratory-based gait entropy assessment. Bouts of continuous walking will be identified from both accelerometer recordings based on activity intensity, and any bouts of at least 1 min will be included in evaluating gait dynamics. Multiscale entropy will be analyzed from each of the gait bouts, and the mean of all bouts will be reported [69, 70].

Hearing acuity. Participants are asked about use of hearing aids. Self-rated hearing is assessed using a question “How is your hearing?”, and it is answered by choosing a number along a continuum between zero (very poor) and ten (very good). Participants using hearing aids evaluate their hearing with and without the aid. In addition, participants are asked whether they are able to hear in a normal conversation with three or more persons with response options: one (yes, without difficulty), two (yes, with some difficulty), three (yes, with a great deal of difficulty), and four (no, not at all). Pure-tone screening audiometry (Oscilla USB-330, Inmedico A/S, Denmark) and Peltor noise reducing headphones with a noise reduction rating of 21 dB are used to measure pure-tone air-conducted hearing thresholds [71]. Hearing thresholds are estimated using the automatic Hughson-Westlake protocol at the frequencies of 0.125, 0.25, 0.5,1, 2, 4, and 8 kHz. Both ears are measured separately. The maximum sound intensity is 90 dB. If the participant does not hear at an intensity of 90 dB, 100 dB is recorded as the hearing threshold.

Visual acuity. Self-rated vision is assessed by asking about the use of spectacles, and if yes, what kind of spectacles with response options: one (reading glasses), two (glasses for farsightedness), three (glasses for reading and farsightedness), four (multifocal glasses), and five (other). Near vision is assessed by asking whether the participant is able to read normal newspaper text. Far vision is assessed by asking whether the participant is able to watch television from a normal watching distance (three meters). The response options are: one (yes, without difficulty), two (yes, with some difficulty), three (yes, with a great deal of difficulty), and four (no, not at all). Binocular visual acuity is assessed first without and then with the participant’s own spectacles. Illuminated Landolt ring chart (Oculus 4512) at a 5 meter distance is used for assessment. The Landolt rings are widely accepted as the standard of reference in measuring distance visual acuity [72].

Respiratory function is assessed with spirometry (Medikro Pro spirometer, Medikro Oy, Kuopio, Finland) in a standing position with a nose clip. Firstly, vital capacity (VC) maneuver is performed two to four times. Participants inhale maximally and exhale into a flow transducer of the spirometer and continue until their lungs are completely empty. Secondly, forced vital capacity (FVC) maneuver is performed at least two times. Participants inhale maximally and exhale fast and forcefully into the flow transducer and continue until their lungs are completely empty. Both VC and FVC maneuvers are discontinued once they meet the criteria of the ATS/ERS Taskforce [73] or when a total of eight exhalations is reached. The highest volume of VC, FVC and the forced expiratory volume in 1 second (FEV1) are recorded in liters, and the peak expiratory flow (PEF) is recorded in liters/second.

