#### Physical activity

*Physical activity surveillance*. Willing participants wear two activity monitors continuously for 7 to 10 days during the time between the home interview and the assessments in the research center. The monitors to be worn are a tri-axial accelerometer (13-bit ±16 g capable of recording 10 days on one charge, UKK RM42, UKK Terveyspalvelut Oy, Tampere, Finland) and an ECG recorder which also includes a tri-axial accelerometer (14-bit ±16 g capable of recording 4 days on one charge, eMotion Faros 180, Bittium Corporation, Oulu, Finland). Both accelerometers are set to sample 100 samples per second. The accelerometer is attached to the anterior aspect of the mid-thigh of the dominant leg. The ECG recorder is attached with an adhesive strip that includes two electrodes 12 centimeters apart. The strip is attached either on the sternum or diagonally on the left side of the chest under the breast to ensure comfortable wear depending on the anatomy of the participant. The monitors are covered with a self-adhesive film for waterproofing. While wearing the monitors, participants complete a diary where they record occasions and reasons for removing the device(s), and their participation in any form of exercise other than walking, specifying the mode of exercise and the time. Participants wear the devices during the orthostatic test, and the cognitive and walking tests at the research center. Participants, who do not wear the activity monitors at home, are supplied with an accelerometer and ECG recorder with an electrode belt for their testing session at the research center.

*Accelerometry.* Movement and non-movement behaviors will be analyzed from both of the tri-axial accelerometer recordings [28]. Physical activity and sedentary behavior will be quantified as the amount of minutes spent at a particular activity intensity level (e.g. sedentary, light, moderate, vigorous). We will explore the usefulness of different bout durations, and gradations of intensity classification (e.g. a hundred possible intensity levels instead of the four conventionally used) in describing physical activity and sedentary time of older people [29, 30].

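### Home gait entropy is averaged over bouts of unequal length and compared with a six-minute laboratory walk, so part of any difference may reflect record length

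*Protocol article*

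**What the plan says.** All of this stands in the Protocol article, under Measures.

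- **Home record.** Under Physical and sensory function, walking bouts are picked out of the multiple-day accelerometer recordings, and "any bouts of at least 1 min will be included in evaluating gait dynamics". There is a floor of 1 min and no ceiling.
- **Home summary.** "Multiscale entropy will be analyzed from each of the gait bouts, and the mean of all bouts will be reported". No common length, windowing or weighting by length is given.
- **Purpose.** The home analysis is described as "enabling comparison with laboratory-based gait entropy assessment".
- **Laboratory record.** The walk lasts six minutes: "The total distance walked by participants in 6 min is measured". Gait characteristics, multiscale entropy among them, "will be assessed from each of the applicable sensors, and from the thigh-worn accelerometer and the chest-worn accelerometer".
- **Sampling rates.** The body-worn sensors used only in the laboratory record at 400 samples per second. For the two accelerometers worn at home, the Physical activity section says "Both accelerometers are set to sample 100 samples per second", and it adds that these devices are also worn during the walking tests.

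**The concern.** Multiscale entropy averages a series in blocks of s samples (scale s) and then counts how often short patterns recur within a tolerance. Two features make it sensitive to record length. A short record leaves few points at long scales. Also, where the tolerance is set as a fraction of the record's own standard deviation, a longer record that holds more slow variation gets a wider tolerance.

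A person's home value may come mostly from bouts of one or two minutes, while the laboratory value comes from a record of up to six. The same gait could then yield two different entropies. A reader who sees a home-laboratory difference could not tell how much is due to the setting and how much to record length. Because the sign of the shift depends on the signal, no known offset can remove it afterwards.

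**Working it through.** The plan gives no figure for this comparison, so there is none to reproduce. The check asks whether record length alone moves the measure when gait is identical.

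**Inputs from the Protocol article:** minimum home bout 1 min; laboratory walk 6 min; accelerometer rate 100 samples per second.

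**Assumed, because the article gives none:** template length m = 2; tolerance r = 0.2 × SD of the record, held fixed across scales; scales 1 to 40; whole six minutes used in the laboratory; every home bout exactly 1 min, chosen as an extreme case.

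**Step 1. Points left after coarse-graining** = seconds × rate ÷ scale.

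| Scale | 1 min | 6 min |
|---|---|---|
| 1 | 60 × 100 ÷ 1 = 6,000 | 360 × 100 ÷ 1 = 36,000 |
| 10 | 600 | 3,600 |
| 20 | 300 | 1,800 |
| 40 | 150 | 900 |

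**Step 2. Same record, two lengths.** A simulated six-minute record was analysed whole and again as six 1-min pieces whose entropies were averaged, with 20 replicates per signal type. Any difference is due to length alone. The synthetic gait signal was quasi-periodic, with stride times near 1.1 s and 1/f variation in stride time and amplitude. Percentages were taken before rounding.

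| Scale | Gait, 6 min | Gait, mean of 1-min pieces | Gait, shift | 1/f noise, shift | White noise, shift |
|---|---|---|---|---|---|
| 1 | 0.901 | 0.900 | −0.1% | +5.5% | 0.0% |
| 5 | 0.789 | 0.770 | −2.4% | +5.5% | +0.1% |
| 10 | 0.750 | 0.713 | −5.0% | +5.1% | +0.1% |
| 15 | 0.485 | 0.449 | −7.3% | +5.5% | +0.2% |
| 20 | 0.652 | 0.610 | −6.5% | +5.0% | +0.4% |
| 40 | 0.578 | 0.568 | −1.7% | +5.7% | +1.0% |

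Summed over all eight scales run (1, 2, 5, 10, 15, 20, 30, 40), the gait signal shifted by −3.2%. At scales 10, 15 and 20 its absolute shifts were 0.038, 0.035 and 0.042 (standard errors 0.005, 0.005 and 0.007). The SD between simulated six-minute records was 0.029, 0.026 and 0.040. That SD describes repeats of one simulated process, not real people.

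**Step 3. Sensitivity to the assumed signal.** Other synthetic gait signals, under the same m and r, gave different sizes and signs.
- A stationary sum of stride harmonics plus noise gave 0.634 v 0.615 at scale 10 (+3%) and 0.696 v 0.663 at scale 20 (+5%), 1 min against 6 min.
- The same signal with slow drift in pace and amplitude gave 0.685 v 0.819 and 0.740 v 0.885, about −16% at both scales. The drift was an assumption, so this figure is illustrative only.
- A further simulation of identical gait gave about −1% to −8% without drift and more with drift.

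**Step 4. If entropy were taken on stride intervals instead of the acceleration signal.** At an assumed 1.1 s per stride, 1 min holds about 55 strides and 6 min about 327. In 300 simulated series, sample entropy was undefined for 7%, 47% and 78% of the 1-min series at scales 1, 2 and 3, and for none of the 6-min series at scales 1, 2, 3 or 5.

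**The case against.** **Settings are left to sources.** The article cites method papers for entropy and, as a condensed account, may leave template length, tolerance and scale range to them or to a fuller plan. That stands, and their absence is no part of this point. The point rests on the rule that the article does state: any bout from 1 min up, one value per bout, the mean reported, compared with the laboratory.

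**The comparator is partly inferred.** The article does not say that all six minutes enter a single entropy calculation, nor whether mean levels or correlations will be compared. This stands too. A constant offset would not disturb a correlation. The offset is constant only if people have similar bout lengths, and the article gives no bout-length distribution.

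**Other differences remain.** The laboratory course turns at cones 19.66 m apart, and equal windows will not remove that contrast with home walking. True; the fix addresses record length only.

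A reader might also infer three stronger things that the document does not support.

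- *That sampling rates are mismatched.* The laboratory-only sensors do record at 400 samples per second, so one scale factor would span a quarter of the time that it spans at 100. But the laboratory analysis also covers the thigh and chest accelerometers worn at home, at 100 samples per second. A same-device comparison is already available, and nothing says that home values will be set against the 400 Hz sensors.
- *That bout length confounds the age and functional-capacity contrasts.* The sentence about detecting such changes follows the six-minute-walk measures and precedes the home recordings. It most naturally refers to the laboratory data. The only stated use of home entropy is the comparison with the laboratory.
- *That the bias is about 16%.* That size appears only under an assumed drift; it is not an estimate for this study.

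**Conclusion.** The point holds in a limited form. The stated rule does not hold record length equal, and record length alone can move multiscale entropy for correlated, gait-like signals. In the main simulation the shift was close to zero at scale 1 and about 5% to 7% at scales 10 to 20 for the synthetic gait signal, about +5% to +6% across scales for 1/f noise, and at most 1% for white noise. The conclusion is that part of a home-laboratory difference may be artefact. Neither its direction nor its size in this study can be predicted.

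This rests on m = 2, r = 0.2 SD, synthetic signals, use of the whole six minutes, and the extreme case of 1-min home bouts. The length effect vanishes if bouts last as long as the laboratory record.

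The consequence is small. The Main outcomes section does not name gait entropy, Table 1 shows gait characteristics as unavailable in the historic cohort, and no sample size depends on this comparison. It is a minor improvement to an exploratory measure.

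**What to change.** State in the gait-characteristics text that:

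1. home bouts and the six-minute walk are both cut into non-overlapping windows of one fixed length, for example 1 min, which is the plan's own minimum and so excludes no eligible bout;
2. entropy is computed per window and the windows are averaged within person, separately for home and laboratory;
3. the home-laboratory comparison uses the same accelerometer in both settings, thigh with thigh or chest with chest, at 100 samples per second;
4. the scale range is limited to what the window supports (1 min leaves 300 points at scale 20 and 150 at scale 40).

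With equal windows the record-length component is removed by construction. The Resilience section already does the equivalent for heart rate variability, which uses five-minute epochs both in daily life and in the research-center tests.

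The cost is a few lines of text and some programming; no new data are needed. The partial window at the end of each bout is lost, always less than one window. Long scales are given up or estimated less precisely. Averaging windows instead of bouts also gives longer bouts more weight, which should be said openly. If entropy is meant to be taken on stride intervals, 1-min windows would be too short and a longer common window would be needed, at the price of excluding shorter bouts.
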